**Technical Summary**

Challenging behaviours can include physically, verbally or sexually aggressive, destructive or self-injurious behaviour. The estimated prevalence of challenging behaviour problems in intellectual disabilities in large population studies shows considerable variation between 4–22%, with multiple factors likely to underlie challenging behaviours in this population. Risk factors associated with challenging behaviours in people with intellectual disabilities include male gender, severe/profound level of intellectual disabilities, co-occurring autism and deficits in receptive and expressive communication. An association with behavioural, psychiatric and psychosocial factors has also been established, but physical conditions such as pain, sleep problems, constipation, epilepsy, urinary/bowel incontinence and sensory impairments have been less studied and existing evidence is mostly of low quality and inconclusive. In this study, we will investigate the incidence of challenging behaviours in a large nationwide population of primary care patients with intellectual disabilities in England. Using stratified Cox proportional hazard models, we will also examine the association between challenging behaviours and physical conditions (i.e. pain, sleep problems, constipation, epilepsy, urinary/bowel incontinence and sensory impairments) in this population, including exploring how different health (e.g. severity of intellectual disabilities, co-occurring autism/genetic syndromes/mental comorbidities), demographic (e.g. age, gender, ethnicity) and socioeconomic (e.g. Practice/Patient Level Index of Multiple Deprivation) factors may affect this relationship.

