**Outcomes to be measured**

Primary outcome: challenging behaviours as defined through READ codes in Appendix 1

Moderator: record of co-occurring physical conditions (i.e. pain, sleep problems, constipation, epilepsy, urinary/bowel incontinence and sensory impairments) as defined through READ codes

Mediators: severity of intellectual disabilities, co-occurring autism/genetic syndromes/mental comorbidities as defined through READ codes in Appendix 1

Confounding covariates: demographic (age, gender, ethnicity) and socioeconomic (Practice/Patient Level Index of Multiple Deprivation) factors

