## **Planned use of linked data and benefit to patients in England and Wales**

Our analysis will use the Clinical Practice Research Datalink (CPRD) GOLD and Aurum databases which will be anonymised. Patients' GP records will be linked with:

1. HES Admitted Patient Care to test for interaction effects with the effect modifier of physical conditions;
2. Mental Health Services Data Set (MHSDS), available for the period of April 2007-November 2015, to assess any attenuation in the associations between the mental comorbidities moderator and challenging behaviours;
3. Practice and Patient Level Index of Multiple Deprivation to adjust for confounding effects of socioeconomic deprivation for all analyses.

**Importance/impact:** This project will extend the existing work on challenging behaviours in people with intellectual disabilities by using nationwide CPRD data to investigate the incidence of challenging behaviours in a large nationwide population of primary care patients with intellectual disabilities in England. Using stratified Cox proportional hazard models, we will also examine the association between challenging behaviours and physical conditions (i.e. pain, sleep problems, constipation, epilepsy, urinary/bowel incontinence and sensory impairments) in this population, including exploring how different health (e.g. severity of intellectual disabilities, co-occurring autism/genetic syndromes/mental comorbidities), demographic (e.g. age, gender, ethnicity) and socioeconomic (e.g. Practice/Patient Level Index of Multiple Deprivation) factors may affect this relationship. The proposed study will provide a much-needed foundation for future research and intervention development designed to reduce health inequalities experienced by patients with intellectual disabilities through better management of challenging behaviours and improved understanding of their association with physical health problems in this population. This is particularly important in the light of lack of existing evidence in this area of research.

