## **Exposures, outcomes and covariates**

Exposure: record of intellectual disabilities

The exposure variable will be a record of intellectual disabilities. Patients with intellectual disabilities will be identified using searches for any code included in Appendix 1, as has been done previously with CPRD (Carey et al. 2016; 2017).

Primary outcome: challenging behaviours

Outcome variables will be presence of challenging behaviours, which will be identified by Read codes in Appendix 1 (Sheehan et al. 2015; ).

Moderator: record of co-occurring physical conditions

Patients with intellectual disabilities and co-occurring physical conditions (i.e. pain, sleep problems, constipation, epilepsy, urinary/bowel incontinence and sensory impairments) will be identified using searches for any relevant READ code, as has been done previously with CPRD (e.g. Glover et al. 2017; Hosking et al. 2016).

Mediators:

severity of intellectual disabilities, co-occurring autism/genetic syndromes/mental comorbidities will be identified using searches for any code included in Appendix 1 (e.g. Glover et al. 2017; Hosking et al. 2016; Houghton et al. 2018)

Confounding covariates:

Demographic (age, gender, ethnicity) and socioeconomic (Practice/Patient Level Index of Multiple Deprivation) factors

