### **Phase 2**

The main statistical analyses will be conducted using stratified Cox proportional hazard models (Sjolander & Greenland 2013). The Cox models will be run univariately, then multivariably. The multivariable analysis will comprise (i) adjustment for demographic (age, gender, ethnicity) and socioeconomic (Practice/Patient Level Index of Multiple Deprivation) factors, (ii) the addition of mediators (i.e. severity of intellectual disabilities, co-occurring autism/genetic syndromes/mental comorbidities) factors) to the above model to assess any attenuation in the associations (iii) the use of likelihood ratio tests to test for interaction effects with the effect modifier (i.e. physical conditions including pain, sleep problems, constipation, epilepsy, urinary/bowel incontinence and sensory impairments) if there is sufficient statistical power and if found to be statistically significant, further sub-group analyses. We will test for proportional hazards in the Cox models using both graphical methods and a formal statistical test based on Schoenfeld residuals. Where the assumption of proportional hazards is violated, we will augment the models with time varying covariates. To account for patients with multiple events over the 10-year study period and investigate incidence rate ratios, we will conduct a Poisson regression, similarly to the methodology applied by Sheehan et al. (2015).

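### Mental comorbidities are labelled mediators, left out of the confounder-adjusted model and given no time order, so step (i) may be confounded and the step (i) to (ii) attenuation cannot be read as mediation

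*Protocol*

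**What the plan says.** **Role.** Outcomes to be measured states: "Mediators: severity of intellectual disabilities, co-occurring autism/genetic syndromes/mental comorbidities as defined through READ codes in Appendix 1". Exposures, outcomes and covariates repeats the label and gives the ascertainment: "severity of intellectual disabilities, co-occurring autism/genetic syndromes/mental comorbidities will be identified using searches for any code included in Appendix 1". Physical conditions, in the same section, "will be identified using searches for any relevant READ code". Neither sentence carries a date rule.

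**Models.** In Phase 2, step (i) is "adjustment for demographic (age, gender, ethnicity) and socioeconomic (Practice/Patient Level Index of Multiple Deprivation) factors". Step (ii) adds the mediators "to the above model to assess any attenuation in the associations". The Plan for addressing confounding lists only sex, age, ethnicity and deprivation.

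**Other roles for the same variable.** The linked-data section plans to use the Mental Health Services Data Set to assess "attenuation in the associations between the mental comorbidities moderator and challenging behaviours". Research question 3 treats mental comorbidities as determinants of incidence, and Phase 1 uses them to stratify incidence.

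**Background.** On challenging behaviours, the Technical Summary says: "An association with behavioural, psychiatric and psychosocial factors has also been established".

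**The concern.** A mediator has to arise after the physical condition and before the outcome. Mental illness can fall at three points. Before the physical condition it may be a common cause, for example depression that leads both to sleep problems and to challenging behaviour. Between the two it may mediate. After the behaviour it may be a consequence, because the behaviour can prompt psychiatric assessment. A single undated indicator merges the three.

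Two answers are at stake. For question 2, step (i) would leave prior mental illness uncontrolled, and a drop at step (ii) caused by removing that confounding would look like mediation. For question 3, any codes dated after the outcome would distort the estimated effect of mental comorbidity itself.

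The label fits the other listed factors even less well. Genetic syndromes are congenital, autism and severity of intellectual disabilities are developmental, and all generally precede the physical conditions.

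**Working it through.** **The plan's own figures.** 3,020,680 + 13,285,111 = 16,305,791. Multiplied by 0.005 this is 81,528.96, stated as 81,529. 81,529 × 0.165 = 13,452.3, stated as 13,452. Both reproduce. The point does not turn on them, and the protocol has no figure that sizes the bias.

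**The roles side by side.** Outcomes to be measured, Exposures and Phase 2 say mediator; the linked-data section says moderator. A moderator calls for an interaction term and a mediator for a step-wise comparison with a time order. The linked-data sentence uses the first word and describes the second analysis.

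**Time order.** In Definition of the study population, a patient with challenging behaviour recorded before 2009 is indexed at 1/1/2009. A psychiatric code can therefore follow the first behaviour record and still precede the index date. Nothing in the text excludes it.

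**Step (i), analytic.** Assumed inputs, none from the documents: 25% have prior mental illness, sleep problems occur in 20% with it and 10% without, its hazard ratio for challenging behaviour is h = 2.5, and sleep problems have no true effect.

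- Share with prior illness among those with sleep problems: 0.25×0.20 / (0.25×0.20 + 0.75×0.10) = 0.05/0.125 = 0.400.
- Share among those without: 0.25×0.80 / (0.25×0.80 + 0.75×0.90) = 0.20/0.875 = 0.229.
- Bias factor (1+(h−1)p1)/(1+(h−1)p0) = 1.600/1.343 = 1.19.

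Over a grid with p0 = 20%, p1 = 30% to 50% and h = 1.5 to 3, the factor runs from 1.15/1.10 = 1.05 to 2.0/1.4 = 1.43.

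**Steps (i) and (ii), simulated.** Same inputs, 20,000 patients, 10 years of follow-up, about 16% with an event. Step (i) gives about 1.18 to 1.20. Adjusting for prior illness only gives 0.98 to 1.03, a spread that shows the simulation noise. Adjusting for an indicator that ignores dates gives:

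| Cases gaining a later code | All patients gaining an unrelated later code | Hazard ratio, physical condition (true 1.0) | Hazard ratio, mental illness (true 2.5) |
|---|---|---|---|
| 30% | 0 | 0.89 to 0.92 | 4.5 to 4.8 |
| 10% | 0 | 0.95 to 0.97 | about 3.1 |
| 30% | 10% | 0.97 to 0.99 | about 3.8 |
| 30% | 20% | about 1.00 | about 3.3 |
| 10% | 20% | about 1.06 | about 2.3 |

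With a true hazard ratio of 1.5, step (i) gives about 1.72 to 1.76 and the undated step (ii) gives 1.33 to 1.58.

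**The case against.** The strongest reply is that the protocol is silent on dates and has not decided to ignore them. The phrase about any code describes the breadth of the code list, Appendix 1 is not shown, and look-back windows commonly sit in a statistical analysis plan. This stands against one tempting reading, that codes will be taken at any date, including after the outcome. The text does not say so. It does not rescue the role, the step (i) adjustment set, the confounder list or the moderator label, all of which the protocol fixes. A date window elsewhere would not change them.

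Second, where mental illness came first, step (ii) is the confounder-adjusted model, and both steps are reported. That is correct. A reader might infer that step (i) is confounded and step (ii) over-adjusts as a matter of fact, but each depends on when the codes fall. The change between the steps still cannot be called mediation.

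Third, the Technical Summary supports only a link between psychiatric factors and the outcome. Confounding also needs a link with the physical condition, which the documents do not give. That link is an assumption here.

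Fourth, a reader might infer that mental comorbidities appear only as a mediator. That holds for the Cox steps but not for question 3, Phase 1 or the linked-data section.

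**Conclusion.** The concern holds in a conditional form. As written, the plan leaves prior mental illness out of its confounder-adjusted model, gives the same variable conflicting roles, and would describe any drop at step (ii) under a mediator label that the missing time order cannot support. For genetic syndromes, autism and severity of intellectual disabilities the label is not tenable.

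The size is illustrative and rests wholly on assumed inputs. At a true null, step (i) shows about 1.18 to 1.20 for the main scenario (1.05 to 1.43 over the analytic grid). If undated codes were used, step (ii) would show about 0.89 to 1.06, and the mental-illness hazard ratio would lie between 2.3 and 4.8 against a true 2.5.

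A reader might infer that step (ii) always pushes the estimate below its true value and always inflates the mental-illness effect. The figures do not support that. The largest distortion needs no patient without challenging behaviour to gain a new psychiatric code in 10 years; once some do, it shrinks or reverses. The defect should be corrected before analysis, but it does not invalidate the study.

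**What to change.** 1. Put mental comorbidity coded before cohort entry, or before the first code of the physical condition, into the confounder-adjusted model together with severity of intellectual disabilities, autism and genetic syndromes as baseline covariates. State which of the two dates applies. Patients without a physical condition have no first code, so cohort entry is the simpler anchor.
2. If attenuation is to be described as mediation, use only new mental-health codes after the physical condition and before the first challenging-behaviour code, as a time-updated covariate.
3. Do not use codes dated on or after the first challenging-behaviour record, including for patients whose behaviour was recorded before their index date.
4. Give each factor one role, and reconcile the linked-data section with Outcomes to be measured, Exposures, Phase 2 and the Plan for addressing confounding.

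The cost is some extra programming and a few sentences; code dates should already be in the records. Patients without an earlier dated code will count as unaffected, so some confounding by unrecorded illness will remain. The Mental Health Services Data Set is available only to November 2015, so new codes after that rest on the other sources.

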## **Data/statistical analysis**

The analysis will be performed using STATA/SPSS Software. In our main analyses, patients will be stratified into subgroups by age, sex and co-occurring intellectual disabilities. All of the analyses as described below will be performed for each subgroup.

### **Phase 1**

We will calculate the incidence of challenging behaviours within the group with intellectual disabilities. Our binary outcome will be defined on the basis of having a record of a relevant Read code for co-occurring challenging behaviours (Appendix 1). Records will be stratified by age, sex, severity of intellectual disabilities and/or co-occurring physical conditions/autism/genetic syndromes/mental comorbidities if cell sizes allow. Tables of baseline characteristics will be described for all patients with intellectual disabilities. For continuous data, mean, median, range, and standard deviations will be calculated. For categorical variables, frequency and percentages will be reported.

### **Phase 2**

The main statistical analyses will be conducted using stratified Cox proportional hazard models (Sjolander & Greenland 2013). The Cox models will be run univariately, then multivariably. The multivariable analysis will comprise (i) adjustment for demographic (age, gender, ethnicity) and socioeconomic (Practice/Patient Level Index of Multiple Deprivation) factors, (ii) the addition of mediators (i.e. severity of intellectual disabilities, co-occurring autism/genetic syndromes/mental comorbidities) factors) to the above model to assess any attenuation in the associations (iii) the use of likelihood ratio tests to test for interaction effects with the effect modifier (i.e. physical conditions including pain, sleep problems, constipation, epilepsy, urinary/bowel incontinence and sensory impairments) if there is sufficient statistical power and if found to be statistically significant, further sub-group analyses. We will test for proportional hazards in the Cox models using both graphical methods and a formal statistical test based on Schoenfeld residuals. Where the assumption of proportional hazards is violated, we will augment the models with time varying covariates. To account for patients with multiple events over the 10-year study period and investigate incidence rate ratios, we will conduct a Poisson regression, similarly to the methodology applied by Sheehan et al. (2015).

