## **Objectives, specific aims & rationale**

The aim of this project will be firstly to investigate longitudinal trends in the incidence of challenging behaviours in a nationwide population of primary care patients with intellectual disabilities, using data from the Clinical Practice Research Datalink. We will also investigate if there is an association between physical conditions and challenging behaviours in patients with intellectual disabilities and what the nature and direction of this association may be.

The project aims to answer the following research questions:

1. What is the 1-, 5- and 10-year incidence of challenging behaviours in a nationwide population of primary care patients with intellectual disabilities?
2. Do physical conditions (i.e. pain, sleep problems, constipation, epilepsy, urinary/bowel incontinence and sensory impairments) increase/decrease the incidence of challenging behaviours in primary care patients with intellectual disabilities?
3. To what extent do health factors (i.e. severity of intellectual disabilities, co-occurring autism/genetic syndromes/mental comorbidities) affect the incidence of challenging behaviours in primary care patients with intellectual disabilities?
4. Is the relationship between the presence of physical conditions and challenging behaviours in patients with intellectual disabilities accounted for by demographic (e.g. age, gender, ethnicity) and socioeconomic (e.g. Practice/Patient Level Index of Multiple Deprivation) factors?

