### Sample size considerations

As per details provided in the 'Feasibility counts' section, if we assume a 0.5% prevalence of intellectual disabilities as per findings reported by Glover et al. (2019; 2020) using a CPRD GOLD database with a follow-up period of April 2010-March 2014, then within the population of currently registered research acceptable (de-duplicated) patients (N=16,305,791 in total; N=3,020,680 for GOLD database and N=13,285,111 for Aurum database) 81,529 patients would be expected to have intellectual disabilities on any given day. Prevalence studies of challenging behaviours in nationwide primary care samples are lacking, but if we assume that a prevalence of challenging behaviours in a population of people of all ages with intellectual disabilities in England is as described in a study of seven District Health Authorities in the UK by Emerson et al. (2001), 16.5% (N=13,452) of patients with intellectual disabilities are expected to have any form of challenging behaviours on any given day during the study follow-up period of 2009-2019, with prevalence rates for specific types of challenging behaviours expected to be much higher (e.g., 42.0% for aggressive behaviours). Given the estimated sample size, the study is expected to have sufficient statistical power. References after amendments: Emerson, E., Kiernan, C., Alborz, A., Reeves, D., Mason, H., Swarbrick, R., Mason, L., & Hatton, C. (2001). The prevalence of challenging behaviours: A total population study. *Research in Developmental Disabilities*, 22(1), 77-93.

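### Step (ii) reads attenuation from the change in a Cox hazard ratio, a scale that understates it and can lose or reverse it when mediation is weak

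*Protocol*

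**What the plan says.** The protocol's Phase 2 section sets the effect scale: "The main statistical analyses will be conducted using stratified Cox proportional hazard models". It then sets the order of fitting: "The Cox models will be run univariately, then multivariably". Step (i) adjusts for age, gender, ethnicity and deprivation. Step (ii) adds the factors listed as mediators under Outcomes to be measured, "severity of intellectual disabilities, co-occurring autism/genetic syndromes/mental comorbidities as defined through READ codes in Appendix 1", and the stated purpose is to add them "to the above model to assess any attenuation in the associations".

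No other effect measure is assigned to this comparison. The Poisson rate ratio in the same section is planned for repeated events. No threshold for attenuation is given.

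Two other places bear on the size of the problem. The Technical Summary treats some of the added factors as prognostic: "Risk factors associated with challenging behaviours in people with intellectual disabilities include male gender, severe/profound level of intellectual disabilities, co-occurring autism". Sample size considerations gives the only planning figure for outcome frequency: "16.5% (N=13,452) of patients with intellectual disabilities are expected to have any form of challenging behaviours on any given day".

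**The concern.** Comparing step (i) with step (ii) is informative only if the coefficient would stay put when the added factors carry none of the association. A Cox HR does not have that property. As follow-up proceeds, people with strong risk factors have their event and leave the risk set, and they leave faster in the group with the physical condition. A model that omits those factors therefore gives an HR nearer to 1 than the model that includes them, even when they are equally common in both groups.

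Mediation moves the HR towards 1 on adjustment, and non-collapsibility moves it away from 1. The reported change is the net of the two. At stake is a statement that severity, autism, syndromes or mental comorbidities explain little or none of an association when they explain some of it. The shift does not shrink as the cohort grows.

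**Working it through.** **Planning figures.** (3,020,680 + 13,285,111) × 0.005 = 81,529 patients, and 81,529 × 0.165 = 13,452. Both match the protocol. It states no HR, no incidence and no attenuation rule, so everything below rests on assumptions.

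**Set-up (assumed).** Physical condition in 20%. Conditional HR 1.50. Three binary predictors with prevalences 25%, 25% and 30%. Constant baseline hazard over 10 years, solved to give a chosen overall cumulative incidence. No loss to follow-up.

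**Formula.** Let S1(t) and S0(t) be the shares of the cohort still at risk with and without the condition, averaged over the predictors, and f1(t) and f0(t) the matching event densities. The Cox model that omits the predictors converges to the β that solves

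∫ { f1(t) − [f1(t) + f0(t)] · e^β S1(t) / [e^β S1(t) + S0(t)] } dt = 0.

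The model that includes them returns 1.50. The spurious share of the log HR is 1 − β / ln 1.50.

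**A. Predictors unrelated to the condition (no mediation, no confounding).**

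| 10-year incidence | Predictor HRs 2.5, 2, 2: HR before → after | Share of log HR | Predictor HRs 3, 3, 3: HR before → after | Share of log HR |
|---|---|---|---|---|
| 5% | 1.491 → 1.500 | 1.5% | 1.478 → 1.500 | 3.6% |
| 16.5% | 1.472 → 1.500 | 4.6% | 1.440 → 1.500 | 10.0% |
| 30% | 1.453 → 1.500 | 7.9% | 1.410 → 1.500 | 15.3% |

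Example: 1 − ln 1.472 / ln 1.50 = 1 − 0.954 = 4.6%. With a conditional HR of 1.00 there is no shift at any incidence.

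**B. Real mediation, 16.5% incidence.** Two of the three predictors (those with 25% prevalence) are made more prevalent among people with the condition. The HR after adjustment is 1.500 throughout. The rare-outcome column shows the attenuation free of the artefact.

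| Excess prevalence | Predictor HRs | HR before, rare outcome | HR before, 16.5% |
|---|---|---|---|
| 1 point | 2.5, 2, 2 | 1.528 | 1.498 |
| 1 point | 3, 3, 3 | 1.540 | 1.474 |
| 2 points | 2.5, 2, 2 | 1.557 | 1.524 |
| 2 points | 3, 3, 3 | 1.581 | 1.508 |
| 5 points | 2.5, 2, 2 | 1.645 | 1.604 |
| 5 points | 3, 3, 3 | 1.706 | 1.613 |

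At 5 points the attenuation is understated but plain. At 2 points with predictor HRs of 3, ln(1.508/1.500) = 0.005 remains of ln(1.581/1.500) = 0.053, so about nine tenths is lost. At 1 point the sign reverses, negligibly for the weaker predictors.

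**C. A second set of assumptions.** Four predictors, condition in 30%, conditional HR 1.30. Without mediation at 16.5% incidence, the HR before adjustment is 1.291 with predictor HRs of 1.5 to 2, and 1.273 with HRs of 2 to 3. One simulated cohort of 81,529 with 13,453 events and the stronger predictors gave 1.254 before and 1.278 after, with a standard error of the log HR of 0.018. The shifts at 16.5% in table A are ln(1.500/1.472) = 0.019 and ln(1.500/1.440) = 0.041, at least as large as that standard error.

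**D. The same comparison on a collapsible scale (set-up C, predictor HRs 2 to 3).**

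| Situation | HR before → after | Risk difference before → standardised after |
|---|---|---|
| 16.5% incidence, no mediation | 1.273 → 1.300 | 0.0376 → 0.0376 |
| 16.5%, two mediators 5 points commoner | 1.432 → 1.300 | 0.0567 → 0.0374 |
| 42% incidence, two mediators 2 points commoner | 1.299 → 1.300 | 0.0828 → 0.0699 |

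The risk difference stays put when nothing is mediated and falls when something is. In the last row the HR shows no change at all.

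**The case against.** The strongest case against is about size and reach, and much of it stands.

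- **Attenuation is not generally hidden.** A reader might infer that step (ii) cannot detect mediation. Table B does not support that: with 5 points of excess prevalence the HR still falls from about 1.60 to 1.50. Near-complete loss or reversal needs weak mediation together with strong predictors or common events. For a condition with no association there is nothing to distort.
- **The event frequency is not the protocol's.** The 16.5% is a point prevalence, used here only as a stand-in for cumulative incidence. The 30% and 42% incidences are illustrations. The protocol quotes prevalences of 4-22% and, under Limitations of study design, expects under-recording. At 5% incidence the shift is trivial.
- **Predictor strength is assumed.** The protocol gives direction only, and partly for specific behaviours.
- **Research question 4.** A reader might extend the point to the question "Is the relationship between the presence of physical conditions and challenging behaviours in patients with intellectual disabilities accounted for by demographic" and the demographic and socioeconomic factors it names. That is not supported. No rule ties the question to a change in HR. Among the step (i) covariates the Technical Summary names only male gender as a risk factor, and analyses are also run within age and sex subgroups. Two unrelated covariates with HR 1.5 move the HR only from about 1.495 to 1.500 at 16.5% incidence.
- **Scale is not the only obstacle.** On any scale, a change between nested models equals mediation only under further assumptions. This is correct, and the fix does not remove it.
- **It could be left to the analysis plan.** Partly fair for the details of standardisation. But the protocol itself states the comparison, its purpose and the model that supplies the measure. The Poisson rate ratio is a partial answer at best, because it is not assigned to step (ii).

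**Conclusion.** The point holds for step (ii), at modest size. The change in HR from step (i) to step (ii) contains a systematic component away from 1 that is neither mediation nor confounding, so attenuation is understated whenever the physical condition has a non-null association. Under a conditional HR of 1.50 and predictor HRs of 2 to 3, that component is about 1.5-4% of the log HR at 5% cumulative incidence, 5-10% at 16.5% and 8-15% at 30%. It matters mainly for a conclusion of little or no attenuation. A clearly visible fall in the HR can still be taken as a fall, though an understated one. These figures rest on assumed predictor strengths, prevalences and incidence, since the protocol supplies none of them. This is an inexpensive improvement to a stated analysis and does not undermine the study as a whole.

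**What to change.** In Phase 2, for the main step (i) and step (ii) models, add standardised cumulative-incidence differences (or ratios) by physical condition at 1, 5 and 10 years, averaged over the same cohort's covariate distribution, with bootstrap intervals for the change between the two models. Base statements about attenuation on these. Keep the HRs as the description of association. The three horizons are those of research question 1, and no new data are needed.

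The cost is some wording plus programming and computing time. That is not trivial where models are stratified or augmented with time-varying covariates, which is why the addition is limited to the main models and not asked of every subgroup. The text should also say that a change on this scale does not by itself separate mediation from confounding.
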